### Randomization and blinding

The concealed randomization schedule will be established using a computer-generated random number sequence, and maintained by an offsite investigator who is neither involved with the enrollment nor with the assessment of study participants. A second research assistant will consecutively open consecutively numbered, randomly ordered, opaque envelopes containing the group allocation (in a 1:1 ratio) after the baseline assessment. All the participants will receive rehabilitation along with 45 min of physical therapy three times a week for 5 weeks after tDCS application. The tDCS will be applied three times a week for 5 weeks for a total of 15 sessions, wherein the patient is evaluated before the beginning of the first session and 1 week after the last session by a blinded investigator.

### Intervention

The tDCS will be applied in accordance with the technique used by Sparing et al. [40]. The patient will be placed in a room with minimal external influences (noise, lamps, and electromagnetic waves), and positioned in a sitting posture with their arms and torso supported on a table at 45°. For stimulation of the right and left posterior parietal lobes, after shaving and cleansing the skin with alcohol, the electrodes will be placed in positions P4 and P3 of the 10/20 International System of Electroencephalography. The reference electrodes will be placed on the cranial vertex (Cz). Four groups of patients will receive stimulation as follows: group 1, right anodal stimulation (P4 anode, reference Cz), group 2, sham control for right anodal stimulation (P4 anode, reference Cz), group 3, left cathodal stimulation (P3 cathode, reference Cz), and group 4, sham control for left cathodal stimulation (P3 cathode, reference Cz). For stimulation, sponge surface electrodes (5 cm × 5 cm square) will be soaked in saline. A continuous current of 1 mA in intensity and a resistance of less than 10 kΩ will be applied for 1200 s with ramping up for 30 s and ramping down for 30 s according to international safety guidelines [38]. The tDCS will be applied using an electrical stimulator, namely the battery-powered DC-Stimulator Plus model, NeuroConn®.

A total of 15 sessions will be performed using a schedule of three times a week for 5 weeks, wherein a blinded examiner evaluates the patient before the beginning of the first session and 1 week after the last session. For the control group (sham), patients will be placed in the same room and position, but the current that will be applied to each control group will be shut off after 30 s.

The physiotherapy protocol will be delivered after tDCS and will be composed of saccadic eye movement training with visual scanning exercises (VSEs) integrated with task-specific activities. The VSEs integrated with task-specific activities will consist of dual-task activities, which require the ability to allocate information-processing resources between two tasks and to maintain sufficient attention on the visual scanning task during the dual-task performance. The guideline of the VSEs integrated with task specific activities and the principles of progression of these exercises follow van Wyk et al. [45], with session durations of approximately 45 min.

### Primary outcome measures

Change in the degree of USN will be measured as follows: (1) D1, as the percentage of changed in range of BIT-C, and (2) D2, based on the CBS.

### Secondary outcome measures

Disability, autonomy, and quality of life will be measured as follows: (1) D3, as the change in neurological status based on the NIHSS, (2) D4, as the change in functional independence based on the Barthel Index, (3) D5, as the change measured using the mRS, and (4) D6, as the change in quality of life based on the EuroQol-5D. For all of the outcomes (except for D6), the change after stimulation will be calculated as follows: 100 (*Vf* − *V0*)/*V0*, where *V0* is the value of the prerandomization variable and *Vf* is the variable value after 1 week of treatment.

### Adverse effects

Any adverse effects will be reported during the study period by the safety questionnaire proposed by Brunoni et al. [46].

### Baseline assessments

#### USN evaluation

*Conventional Behavior Inattention Tasks (BIT-C)*: the six conventional tasks of the BIT-C will be administered, consisting of Star Cancellation (SC), Letter Cancellation (LC), Line Crossing (LiC), Line Bisection (LB), Figure and Shape Copying (FSC-A&B), and Representational Drawing (RD). The BIT-C is usually administered to diagnose USN and provides a range (0–146) and a cutoff score. For all USN tests, the examiner will place the test sheet in front of the patient with a distance of 60 cm between the paper and the glabella of the patient [47].

*Catherine Bergego Scale (CBS)*: this test will be used to measure the extent to which the USN interferes with daily tasks. The scale is divided into 10 activities each with a score of 0 to 3. The maximum scale score is 30 and the total indicates USN severity [27].

#### Neurological and functional evaluation

*Mini-mental State Examination (MMSE)*: this instrument is used for screening cognitive function, and provides measures of orientation, registration (immediate memory), short-term memory (but not long-term memory) as well as language functioning. Scores of 25–30 out of 30 are considered normal; the National Institute for Health and Care Excellence (NICE) classifies 21–24 as mild impairment, 10–20 as moderate impairment, and <10 as severe impairment. The MMSE is used in this trial for data characterization [48].

*Edinburgh Handedness Inventory (EHI)*: the EHI is a measurement scale used to assess the dominance of a person’s right or left hand in everyday activities, sometimes referred to as laterality [49].

*Hospital Anxiety and Depression Scale (HAD)*: the HAD was originally developed by Zigmond and Snaith (1983) and it is used to determine the levels of anxiety and depression that a patient is experiencing, being composed for fourteen items. Seven of the items relate to anxiety and seven relate to depression. Each item on the questionnaire is scored from 0 to 3 which means that a person can score between 0 and 21 for either anxiety or depression [50].

*National Institutes of Health Stroke Scale (NIHSS)*: this test will be used to evaluate the effect of acute cerebral infarction on the levels of consciousness, language, neglect, visual-field loss, extraocular movement, motor strength, ataxia, dysarthria, and sensory loss. The higher the score on this scale the greater the neurological deficit [51].

*Functional Independence Measure (FIM)*: this test will be used to measure the functional independence and autonomy of the subjects in six domains (self-care, sphincter control, mobility, locomotion, communication, and social cognition). The scale scores range from 18 to 126, and the higher the score, the better the autonomy and independence [52].

*Barthel Index*: this test will be used to measure the functional independence and autonomy of the subjects in 10 activities, namely, feeding, bathing, personal care, ability to dress, motility, urinary pace, bathroom use, transfer, mobility, and climbing stairs. The maximum score is 100 which indicates a greater degree of autonomy [51, 53].

*Modified Rankin Scale (mRS)*: this test will be used to evaluate the degree of independence, and determines whether the patient can perform self-care during activities of daily living [51]. The scale is ordinal from 0 to 6, and the greater the score, the worse the functional capacity.

*The European (EuroQol 5D) Quality of Life Scale*; this test will be used to measure the impact of stroke on the subject’s quality of life in five domains, namely, structured mobility, self-care, usual activities, pain/discomfort, and anxiety/depression. The scale scores range from 0 to 10, and the higher the score, the worse the perception of life quality. At the end of the test, patients will mark their health on an ordinal scale from 0 to 100, with a lower score indicating poorer health [54].

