### Data analysis

To detect changes in continuous outcomes, a comparison between the anodal tDCS and the cathodal tDCS, as well as between the tDCS and sham stimulation, will be performed using a linear regression model with a normal response. This analysis will be adjusted for potential confounders, such as age, mRS score, and USN score at baseline. This analysis approach does not test the validity of the model’s theoretical assumptions with a normal response. However, if a fault is identified then the comparison will be performed by adjusting the regression model with an asymmetric response. In the latter case, the comparison will be made using the nonparametric Mann-Whitney test. Data will be analyzed using SPSS version 22 (SPSS Inc., Chicago, IL 60606, USA), and will be considered statistically significant at a *p* value < 0.05.

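### The protocol calls the mRS ordinal but defines outcome D5 as a percentage of the baseline grade, so the effect cannot be read in mRS grades and some patients are ranked in the wrong order

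*Protocol article*

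**What the plan says.** All of this is in the protocol article.

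- Neurological and functional evaluation, on the mRS: "The scale is ordinal from 0 to 6, and the greater the score, the worse the functional capacity".
- Secondary outcome measures defines "D5, as the change measured using the mRS" and then gives a common rule: "For all of the outcomes (except for D6), the change after stimulation will be calculated as follows", namely 100(Vf − V0)/V0, where V0 "is the value of the prerandomization variable". Only D6 is exempt, so D5 is covered.
- Data analysis opens with "To detect changes in continuous outcomes, a comparison between the anodal tDCS and the cathodal tDCS" and says that this comparison, like that of tDCS with sham, "will be performed using a linear regression model with a normal response". It adds: "This analysis will be adjusted for potential confounders, such as age, mRS score, and USN score at baseline". It also says: "This analysis approach does not test the validity of the model’s theoretical assumptions with a normal response".
- The same section goes on to say that, if some fault is found, a regression with an asymmetric response will be used, and it then names the Mann-Whitney test. It does not say what counts as a fault or how one would be found.

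The article states no analysis of the mRS grade itself.

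**The concern.** An ordinal grade orders patients but does not measure amounts. Dividing a change in grade by the starting grade treats the labels as quantities with a true zero, which conflicts with the protocol's own description of the scale. The same improvement then carries a different weight according to where the patient started. The result cannot be translated back into patients moving between grades.

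The Background motivates the trial partly by noting that earlier tDCS studies did not report less long-term disability. D5 is one of the secondary outcomes that address this gap, so an mRS result that cannot be interpreted would weaken the trial there.

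**Working it through.** **Inputs from the protocol article.** The scale runs from 0 to 6, the formula is 100(Vf − V0)/V0, and there are 15 patients per group. The article gives no mRS effect size, baseline distribution or power figure. Its sample size rests on a different outcome, so there is no stated mRS figure to reproduce.

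**1. The formula on the grades (exact, no assumptions).** Entries are D5 in percent.

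| Baseline V0 | Vf=0 | 1 | 2 | 3 | 4 | 5 | 6 |
|---|---|---|---|---|---|---|---|
| 1 | −100 | 0 | +100 | +200 | +300 | +400 | +500 |
| 2 | −100 | −50 | 0 | +50 | +100 | +150 | +200 |
| 3 | −100 | −66.7 | −33.3 | 0 | +33.3 | +66.7 | +100 |
| 4 | −100 | −75 | −50 | −25 | 0 | +25 | +50 |
| 5 | −100 | −80 | −60 | −40 | −20 | 0 | +20 |

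Three things follow.

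- *Unequal weight.* A one-grade improvement is −100/V0 percent. The ratio between grades 1 and 5 is 100/20 = 5. Between grades 2 and 5 it is 50/20 = 2.5.
- *Reversed order.* 5→1 (−80%) ranks below 1→0 (−100%). 5→3 (−40%) ranks below 2→1 (−50%). 5→6, a move to the worst grade, scores +20%, while 1→2 scores +100%.
- *Undefined value.* V0 = 0 gives division by zero. The eligibility criteria set no mRS limit, although grade 0 should be rare in patients with neglect.

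**2. Dependence on the baseline mix.** Suppose every patient improves by exactly one grade. The two mixes below are assumptions.

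- Grades 1 to 5 at 10/20/25/30/15%: 0.10×100 + 0.20×50 + 0.25×33.3 + 0.30×25 + 0.15×20 = 38.8, so a mean of −38.8%.
- Grades 2 to 5 at 15/25/40/20%: 0.15×50 + 0.25×33.3 + 0.40×25 + 0.20×20 = 29.8, so a mean of −29.8%.

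The same clinical change gives two different effects. In the first mix, the 10% of patients at grade 1 supply 10/38.8, about 26% of the mean.

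**3. Power (simulation).** Data were generated with a common odds ratio, tests were two-sided at 0.05, and each of the three models was adjusted for baseline mRS. The odds ratios and baseline mixes are assumptions. Power is in percent for 30 v 30, that is, both active groups against both sham groups.

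| Run and baseline mix | Odds ratio | Percentage, linear | Raw grade, linear | Ordinal |
|---|---|---|---|---|
| A, grades 1–5 | 2.7 | 45 | 52 | 53 |
| A, grades 1–5 | 4.1 | 70 | 80 | 82 |
| A, grades 2–5 | 2.7 | 51 | 53 | 54 |
| A, grades 2–5 | 4.1 | 78 | 79 | 82 |
| B, mostly 3–5 | 2.7 | 49.4 | 53.6 | 64.0 |
| B, mostly 3–5 | 4.5 | 82.7 | 87.2 | 88.0 |
| B, spread 1–5 | 2.7 | 45.6 | 54.2 | 54.0 |
| B, spread 1–5 | 4.5 | 78.5 | 85.3 | 90.0 |
| B, 5% at grade 0 | 2.7 | 43.8 | 52.3 | 57.3 |
| B, 5% at grade 0 | 4.5 | 76.3 | 84.2 | 88.0 |

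Run A used 400 replicates per cell (Monte Carlo error about 2 points). The ordinal figures in run B rest on 150 (about 2 to 4 points). In run B at 15 v 15 and odds ratio 4.5, the percentage model gave 47 to 53% and ordinal regression 60 to 65%. Over both runs and both group sizes, the loss against ordinal regression was about 3 to 16 points.

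In eight of the ten rows, more of the gap closes on moving from the percentage to the raw grade than on moving from the raw grade to the ordinal model. The two exceptions are A, grades 2–5 at 4.1 (1 point against 3) and B, mostly 3–5 at 2.7 (4.2 against 10.4).

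**The case against.** *Normal regression is not the only analysis.* A reader might infer that D5 has nothing but a normal linear model. The documents do not support that: Data analysis limits that model to continuous outcomes and names two fallbacks, one of them a rank test. This stands. In run B at odds ratio 4.5 and 30 v 30, Mann-Whitney on the percentages reached 83 to 84%, against 76 to 83% for the linear model. But the trigger is undefined, the test drops the covariate adjustment, and it would rank the percentages with their reversals. If the restriction to continuous outcomes is read as leaving the mRS out, D5 has no assigned analysis, yet the percentage definition still applies to it.

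*An ordinal model may be in an analysis plan that is not shown.* This stands, so its absence is not the point. The percentage formula is a stated rule.

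*Baseline mRS is a covariate.* It absorbs part of the dependence on starting grade. It does not restore the order of the response: a gain of k grades still scores −100k/V0 percent.

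*The power figures are assumed.* This stands. The data were generated from the model that favours the proposed analysis, and the ordinal test was slightly liberal at 15 per arm (0.059 in 1,500 runs), so part of the gap is not real gain.

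*The fivefold weighting needs patients at grade 1.* This stands. No document says how many there will be.

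**Conclusion.** The point holds for the definition of D5. A scale that the protocol calls ordinal is turned into a percentage of its own label. The unequal weights, the reversals and the undefined case at V0 = 0 follow from the formula alone and need no assumption. A mean D5 cannot be read as movement between grades.

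The loss of power is supporting evidence only. About 3 to 16 points is plausible under the assumed distributions and odds ratios, mostly because of the percentage and not because an ordinal model is lacking.

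Two stronger readings are not supported. The percentage test is not invalid: its type I error stayed at about 4 to 6% in the simulations. The trial's sizing is also not affected, since D5 is secondary and the sample size was based on another outcome. The point should be corrected, but it does not threaten the primary analysis.

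**What to change.** Exempt D5 from the percentage formula, as D6 already is. Analyse the mRS grade at close-out by proportional-odds regression with baseline mRS and the other planned covariates, and report the common odds ratio with a 95% CI and the distribution of grades by group.

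Name in advance a rank test on the grades for use if sparse grades make the model unstable, and state the rule for switching. That test should take account of baseline, for example by stratifying on baseline grade. In run B (30 v 30, odds ratio 4.5), an unadjusted Mann-Whitney test on the close-out grade reached only 59 to 72%, below the percentage model's 76 to 83%.

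The cost is wording in the analysis section. Table 1 already schedules the mRS at allocation and at close-out. The downsides are that the result rests on a common odds ratio across grades, which should be checked descriptively, and that 15 patients per group may leave some grades nearly empty.

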### Data analysis

To detect changes in continuous outcomes, a comparison between the anodal tDCS and the cathodal tDCS, as well as between the tDCS and sham stimulation, will be performed using a linear regression model with a normal response. This analysis will be adjusted for potential confounders, such as age, mRS score, and USN score at baseline. This analysis approach does not test the validity of the model’s theoretical assumptions with a normal response. However, if a fault is identified then the comparison will be performed by adjusting the regression model with an asymmetric response. In the latter case, the comparison will be made using the nonparametric Mann-Whitney test. Data will be analyzed using SPSS version 22 (SPSS Inc., Chicago, IL 60606, USA), and will be considered statistically significant at a *p* value < 0.05.

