**Methods:**

A prospective randomized controlled trial with two parallel groups will be conducted, which will aim to recruit 60 patients with USN after ischemic or hemorrhagic stroke. Participants will be randomly placed into the following four treatment groups: (1) anodal tDCS over the right parietal lobe (*n* = 15), (2) cathodal tDCS over the left parietal lobe (*n* = 15), (3) a sham group of anodal tDCS over the right parietal lobe (*n* = 15), and (4) a sham group of cathodal tDCS over the left parietal lobe (*n* = 15). Blinded assessors will conduct two baseline assessments and one post-intervention assessment. The primary outcome measure will be the level of USN as assessed by the conventional Behavioral Inattention Tasks and the Catherine Bergego Scale. Secondary measures will include neurological capacity (based on the Scandinavian Stroke Scale), functional capacity (based on the Functional Independence Measure and Modified Rankin Scale), autonomy (based on the Barthel Index), and quality of life (based on the EuroQol-5D). Group allocation will be concealed, and all analyses will be based on an intention-to-treat principle.

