### Aims

The principal objective of this study in patients with USN after stroke is to evaluate the efficacy and safety of 15 sessions of tDCS versus placebo in ameliorating USN. We hypothesize that tDCS will induce changes in the neuronal activity of the posterior parietal lobe that will reduce USN presentation in patients after stroke.

In addition, we will assess the effects of tDCS on the capacity of function, level of paralysis, and quality of life.

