### Sample size

We estimate a minimum sample size per group of 15 assuming: simple random sampling; type I and II error probabilities equal 0.05 and 0.20, respectively; the absence of confounders; normal distribution for the outcome “percentage of deviation” with a mean baseline equal to a 15 % reduction in the outcome after tDCS; an estimated reduction of between 8 and 3 % for the sham group; and a variation coefficient of 20 %.

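### Two unranked primary outcomes and an undefined tDCS v sham contrast are all tested at 0.05, so the single 5 % error budget does not hold if any one positive result counts

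*Protocol article*

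**What the plan says.** - **Outcomes.** Primary outcome measures lists "1) D1, as the percentage of changed in range of BIT-C, and (2) D2, based on the CBS". The Abstract (Methods) puts it this way: "The primary outcome measure will be the level of USN as assessed by the conventional Behavioral Inattention Tasks and the Catherine Bergego Scale". Neither place ranks the two instruments or says whether one or both must be positive.
- **Contrasts.** Data analysis plans "a comparison between the anodal tDCS and the cathodal tDCS, as well as between the tDCS and sham stimulation". Intervention describes four arms, with a separate sham for each polarity. Data analysis does not say whether tDCS v sham pools the two active arms and the two shams, or compares each polarity with its own sham.
- **Threshold.** The same section closes with one criterion for the results, which "will be considered statistically significant at a *p* value < 0.05". Sidedness is not stated.
- **Error budget.** Sample size assumes "type I and II error probabilities equal 0.05 and 0.20, respectively" for one outcome and gives 15 per group.
- **Objective.** Aims gives one principal objective, to "evaluate the efficacy and safety of 15 sessions of tDCS versus placebo in ameliorating USN". The Discussion adds a second question: which polarity works better.

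**The concern.** The sample size assumes one test with a 5 % false positive rate. The analysis text leads to at least four tests on primary outcomes (two outcomes by two contrasts), or six if each polarity is compared with its own sham. All of them use the same threshold and none is marked as the lead.

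With 15 patients per arm, one isolated significant result among several is quite likely by chance alone. Without a stated lead test, that result could be presented as the trial's finding at the 5 % level when its real error rate is higher. The open choice between pooled and polarity-specific sham comparisons adds to this, because the choice could be made after the data are seen.

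**Working it through.** **Inputs from the protocol article.** Two primary outcomes (Primary outcome measures); contrasts and threshold 0.05 (Data analysis); four equal arms of 15 (Abstract, Intervention); type I error 0.05 and type II error 0.20 (Sample size).

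**Assumptions not in the article.** No true effect on either outcome in any arm (global null); two-sided tests; success declared on any one significant test; correlation ρ between the BIT-C and CBS changes from 0 to 0.7, with 0.9 as a stress value; normal approximation.

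**Step 1. The plan's own error figure.** One test at 0.05 has a 5 % error rate, as Sample size states. The article gives no family-wise rate to compare with.

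**Step 2. Independent outcomes (ρ = 0).**
- Pooled tDCS v sham, two tests: 1 − 0.95² = 9.75 %.
- Each polarity v its own sham, four tests: 1 − 0.95⁴ = 18.5 %. The two contrasts share no arm, so they are independent.
- Pooled tDCS v sham plus anodal v cathodal, also four tests: 18.5 %. These two contrasts are orthogonal with equal arms.
- Both polarity-specific sham contrasts plus anodal v cathodal, six tests: the contrasts share arms, so the product formula (1 − 0.95⁶ = 26.5 %) overstates the rate. Simulation with the true correlation between contrasts gives 24.2 %.

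**Step 3. Correlated outcomes** (simulation, 1,000,000 draws per value of ρ).

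| Tests counted (both outcomes) | ρ = 0 | ρ = 0.5 | ρ = 0.7 | ρ = 0.9 |
|---|---|---|---|---|
| Pooled tDCS v sham only | 9.75 % | 9.1 % | 8.4 % | 7.0 % |
| Each polarity v its own sham | 18.5 % | 17.3 % | 16.0 % | 13.6 % |
| Pooled tDCS v sham + anodal v cathodal | 18.5 % | 17.3 % | 16.0 % | 13.6 % |
| Each polarity v its own sham + anodal v cathodal | 24.2 % | 22.6 % | 20.9 % | 17.9 % |

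The first two rows concern efficacy against sham. The last two also count a comparison of two active arms.

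**Step 4. One direction only.** If a false claim means tDCS wrongly found better than sham, each test contributes 0.025. At ρ = 0 this gives 1 − 0.975² = 4.9 % (pooled) and 1 − 0.975⁴ = 9.6 % (per polarity). At ρ = 0.7 the figures are 4.2 % and 8.2 %. The matching benchmark for a single test is 2.5 %, so the inflation relative to one test is about the same.

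**Step 5. What adjustment costs.** Fifteen per group gives 80 % power at two-sided 0.05 for a difference of (1.960 + 0.842) × √(2/15) = 1.02 SD. For that difference with 15 per group:
- at 0.025 (the first Holm step for two polarities), power is Φ(2.802 − 2.241) = Φ(0.560) = 71 %;
- at 0.05/4 = 0.0125 (Bonferroni over four tests), power is Φ(2.802 − 2.498) = Φ(0.304) = 62 %, and 80 % would need 22 per group;
- a single lead test at 0.05 loses nothing.

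**The case against.** **The analysis plan may settle this.** A journal article often leaves multiplicity rules to an analysis plan, and none is shown here. The 0.05 threshold may be only a general reporting convention. That is fair as far as missing detail goes, and the article nowhere says that any one significant test wins. But it does itself name two unranked primary outcomes, apply one threshold to several contrasts, and budget a single 0.05. What it states does not fit together without a further rule.

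**The lead contrast is named.** Aims makes tDCS v placebo the principal objective, so it would be wrong to say that nothing indicates which contrast carries the conclusion. This stands. What remains open is which outcome leads and how the sham contrast is formed.

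**A reader might infer a 16–24 % chance of a false efficacy claim.** The documents do not support that. The range counts anodal v cathodal, which has no sham arm and cannot show efficacy against placebo. Its upper end also needs uncorrelated outcomes, although both instruments measure neglect.

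**Both outcomes may be required.** The Abstract speaks of one primary outcome measure assessed by both instruments. If both had to be significant, having two outcomes would cause no inflation. The wording allows this reading but does not state such a rule.

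**Conclusion.** The point holds in a limited form. If any one significant result counts, the two-sided family-wise error for tDCS v sham is about 8–10 % when pooled and 16–18.5 % per polarity, against the 5 % in Sample size. It is 16–24 % only if anodal v cathodal is counted as well. At a correlation of 0.9 the figures run from 7 % (pooled sham contrast only) to 18 % (all six tests).

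The arithmetic is firm. The size depends on the global null, two-sided testing, the any-one-counts reading and the assumed correlation, so no single figure is a property of the plan. Even the narrowest of these any-one-counts cases, one pooled contrast on two outcomes, exceeds 5 %. The defect can be repaired without changing the design.

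**What to change.** Before unblinding, add a few lines to the protocol or analysis plan:

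1. **Lead test.** tDCS v sham on BIT-C, at two-sided 0.05, following the principal objective in Aims.
2. **Form of the contrast.** State whether it is pooled or per polarity. The article supports either: Aims speaks of tDCS as a whole, while Intervention gives each polarity its own sham. If per polarity, apply Holm across the two polarities.
3. **CBS.** Test it only if the lead test is significant. In the per-polarity version, define the gate. A simple valid rule is to go on to CBS, again with Holm, only if both BIT-C contrasts are significant.
4. **Anodal v cathodal.** Label it secondary and report an estimate with a confidence interval. Do not make it depend on CBS, because the Discussion treats it as a question in its own right.

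**Cost.** A result positive on CBS alone, or only in the polarity comparison, becomes supportive. The pooled lead test keeps its full 0.05, but pooling dilutes the effect if only one polarity works. With Holm, power for one polarity can fall from 80 % to about 71 % at the first step, for the effect that 15 per group detects at 0.05.
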